#### Plans to promote participant retention and complete follow-up {18b}

Participants in the intervention and control arm will be shown a short, animated video thanking them for participating in the trial while in the dental setting. The ‘Thank you’ video gives information on what to expect in subsequent follow-up contacts in 6, 12 and 18 months’ time and aims to maximise retention in both control and intervention arms. Shopping vouchers for reimbursement for participants’ time participating in the trial will be posted to their home address and connected to key follow-up contact points (£10 at the 6- and 18-month follow-ups and £15 at the 12-month follow-up point.

#### Data management {19}

Site-specific trial-related information will be stored securely and confidentially at sites and all local relevant data protection policies will be adhered to. Follow-up of participants by phone, email or letter require that participant contact details including name, email address and telephone details are stored. Contact information will be added to the RETURN contact database at trial enrolment and the contact database will be maintained securely on password-protected computers. A data sharing agreement will be in place between the University of Liverpool and NHS BSA to safeguard the confidentiality of personal identifiable data transfer between the two organisations. Leeds University is also considered to be a Joint Data Controller, with respect to the required data for Health Economics analysis. Data will be transferred using a Secure File Transfer platform.

Data queries will be sent via email and through REDCap (the data collection database used in the trial) to site staff. The person responsible for dealing with the data query will be the site Principal Investigator (PI).

### Confidentiality {27}

This trial will collect personal data (e.g. participant names), including special category personal data (i.e. data concerning health) which will be handled in accordance with all applicable data protection legislation. Individual participant health information obtained will be considered confidential and not disclosed to third parties. Case Report Forms will be labelled with the patient’s initials and a unique trial screening and/or randomisation number. Consent forms will be transferred separately to any other trial documentation to ensure the pseudonymisation of special category data is maintained.

#### Plans for collection, laboratory evaluation and storage of biological specimens for genetic or molecular analysis in this trial / future use {33}

No biological specimens are collected in this trial.

### Statistical methods

#### Statistical methods for primary and secondary outcomes {20a}

An extract of the NHS BSA data will be obtained after 12 months (52 weeks) of recruitment. This will aid in the preparation of analysis code before receiving the 18-month (78 weeks) data. Final analysis of the first primary outcome will be conducted on the 18-month data. Analysis of the first primary outcome will involve the number and percentage of participants found to have a planned dental appointment within 12 months which will be reported for each treatment group separately. The denominator will be the number of randomised participants in each treatment group. A comparison between groups will be done using logistic regression, adjusted for the stratification factor site as a random effect (random intercept only). The derived binary variable for attendance for a planned appointment within 12 months will be the dependent variable. The odds ratio and corresponding 97.5% confidence interval will be reported and *p*-value. A sensitivity analysis will be conducted removing all participants from the above primary analysis who were recruited in dental practices (i.e. not randomised at the Dental Hospital) and who do not have a matched NHS BSA record at baseline. This is to assess the impact of including the participants who were not successfully matched in the NHS BSA data at baseline which may indicate that it was possible to get NHS BSA data at later timepoints.

Analysis of the second primary outcome will involve summaries of OHIP-14 scores presented at baseline and 12 months separated by treatment group, for all participants included in this analysis. The OHIP-14 scores at 12 months will be analysed using linear regression, adjusting for the baseline value of OHIP-14 and the stratification factor site as a random effect (random intercept only). The estimated treatment effect and corresponding 97.5% CI will be reported along with the *p*-value. This will be a complete case analysis, only participants with valid baseline and 12-month questionnaires will be included in the analysis.

A second analysis will also adjust for other pre-specified baseline variables, including dental anxiety and socio-economic status.

Analyses will include all randomised participants. The principle of intention-to-treat, as far as practically possible, will be the main strategy of the analysis adopted for primary outcomes and all the secondary outcomes. To allow for joint primary outcomes, the type I error rate will be controlled by setting *α* = 0.025 and therefore confidence intervals (CI) will be presented at 97.5% for both the primary outcomes. No other adjustments will be made for multiplicity. Other secondary outcomes will be reported at the 95% confidence level. *p*-values will be reported to 3 decimal places or 1 significant figure if *p*<0.001. Percentages will be reported to 1 decimal place throughout; continuous baseline characteristics will be presented to 1 decimal place or 1 significant figure and all other values will be present to 2 decimal places or 1 significant figure. All analyses will be performed with standard statistical software (SAS version 9.4 or later). For the purpose of measuring timepoints, 6 months = 26 weeks, 12 months = 52 weeks and 18 months = 78 weeks. A full statistical analysis plan is available from the research team.

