#### Baseline assessments

The following data will be collected by participant self-report prior to randomisation:Demographic information:Sex (Male/female/prefer not to say)AgeEthnicitySocio-economic information:Education levelEmployment status:In paid employment: Yes/NoIf not employed whether: currently looking/ student /retired /not able due to disability/ not currently looking/ otherBenefit status: Yes/No/Prefer not to sayOHIP-14: 14-item oral health-related quality of life questionnaire [33]EQ-5D-5L: 5-item generic quality of life questionnaire [34]Modified Dental Anxiety Scale (MDAS): 5-part dental anxiety questionnaire [35]Protection Motivation Theory: questionnaire measuring psychological mediators [36]Susceptibility of developing urgent dental problemsResponse efficacy for attending for planned care – that this would reduce the chance of developing an urgent dental problemSeverity – not attending for planned dental care means they would be at risk of tooth loss, bad breath, or getting an abscessSelf-efficacy of attending for planned dental careIntention to attend for a planned care appointmentSelf-report of halitosis [37]Self-report of bad taste [38]Prescription information—prescription of antibiotics and/or analgesics for dental problems by a dental, GP or A&E or similar centre within the last 6 months.

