#### Protection motivation theory: psychological mediation

The Protection Motivation Theory (PMT) is based on a premise that there are two alternative responses to threats (such as dental pain) which are either protective or adaptive coping strategies, or maladaptive responses such as avoidance or procrastination [39]. PMT predicts that the primary determinant of adaptive coping strategies such as planned dental visiting is whether or not an individual has formed a protection motivation with regard to the focal behaviour: for example, an intention to act to manage a health threat (e.g. dental pain). This is in turn informed by parallel appraisal processes: threat appraisal and coping appraisal. Threat appraisal variable predictors comprise perceived severity (seriousness) of the health threat, perceived susceptibility (vulnerability) and fear of the health threat. Applied to dental attendance, patients will be asked to consider the severity of their dental pain and their susceptibility for experiencing dental pain. In order to minimise participant burden; MDAS scores will be used as an indicator of fear of the health threat [35]. Coping appraisal variables comprise self-efficacy (i.e. confidence in performing the focal behaviour) and response efficacy. Applied to dental attendance, patients report their confidence they can attend dental appointments and that such attendance would be an effective way to reduce the threat of dental pain

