### Sample size {14}

Twenty six percent of patients attending urgent dental care access centres report they feel attending a dentist regularly is important [40] and other work shows that only 20% of users of such services have their own dentist [41]. Since unpublished data from an NHS evaluation in the North West of England found that an average of 16% of users of urgent dental care services delivered in dental practices returned to a practice for planned dental care over the subsequent 22 weeks, we estimated that over the longer period of 12 months, we might expect 30% of urgent dental care users to return for a planned dental care appointment. The calculation is based on a minimum clinically important difference of 10 percentage points (i.e. an improvement to 40% of patients attending a dentist) in the first of the joint primary outcomes. We estimate there is a possibility of some contamination between patients within practices. Rather than use a cluster randomised design, we have reduced the difference we want to detect to 9 percentage points to allow for potential contamination. Based on this, a sample size of 559 per group would give 80% power at *α* = 0.025 (to allow for joint primary outcomes) to detect this improvement in the intervention group. Allowing for 5% loss to follow-up gives a total target sample size of 590 per group.

For the second primary outcome, OHIP-14, we estimate a standard deviation of 11 points at 1-year follow-up. We also assume a higher rate of loss to follow-up of 20% for this outcome, as it will require successful telephone follow-up. Based on this, our total sample size of 1180 will give 80% power to detect a minimum clinically important difference of 2.25 points, with *α* = 0.025.

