#### Methods for additional analyses (e.g. subgroup analyses) {20b}

Whether there is a differential intervention effect over the socio-economic gradient will be explored. The dependent variable of this analysis will be defined in the same way as was defined for primary and secondary outcomes. This outcome will be analysed in the same way as other outcomes; however, the estimated treatment effect and corresponding 95% CI will be reported (instead of a 97.5% CI) along with the *p*-value. However, the logistic regression model will include IMD, and an interaction between IMD and intervention and an interaction between IMD and site. Other socio-economic factors such as employment status may also be considered, as well as gender and ethnicity, while acknowledging the potential for multicollinearity.

A further analysis of the primary outcome (using logistic regression) will also adjust for the following baseline covariates:Education level (‘No formal qualifications’ will be the reference category)Index of multiple deprivation (IMD)Modified dental anxiety scale (MDAS)

The baseline covariates of education and IMD will be assessed for multicollinearity as they may be correlated. If it is found that there is an association between them, then one of them will be removed.

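### The attendance models leave out baseline intention to attend, which is collected before randomisation, so some power may be forgone (an inexpensive improvement, not an error)

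*Protocol article*

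**What the plan says.** Statistical methods {20a} sets the attendance model: "A comparison between groups will be done using logistic regression, adjusted for the stratification factor site as a random effect (random intercept only". It contains no patient-level covariate. The same section then says, for the co-primary outcomes together: "A second analysis will also adjust for other pre-specified baseline variables, including dental anxiety and socio-economic status".

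Methods for additional analyses {20b} makes this concrete for attendance: "A further analysis of the primary outcome (using logistic regression) will also adjust for the following baseline covariates". The list that follows has three items: education level, deprivation index (IMD) and the dental anxiety scale (MDAS). The only rule for changing it is that education or IMD is dropped if the two are associated.

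Baseline assessments introduces its list with "The following data will be collected by participant self-report prior to randomisation". The Protection Motivation Theory questionnaire is on that list and includes an item on intention to attend a planned care appointment. The section on that theory reports its prediction that "the primary determinant of adaptive coping strategies such as planned dental visiting is whether or not an individual has formed a protection motivation", and gives an intention to act as the example. It also says that MDAS will stand for fear, one of the appraisals that feed into that motivation.

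Elsewhere, intention is used only in between-group t-tests at follow-up and as a mediator (Analysis of psychological variables).

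**The concern.** The further attendance model includes a variable that the theory places upstream (fear, through MDAS) and leaves out the one that it places closest to the behaviour (intention). The OHIP-14 co-primary outcome is adjusted for its own baseline value. Attendance has no baseline value to use, because eligibility requires two years or more without a planned visit, so measured intention is the natural candidate in its place.

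Adjusting a logistic model for a prognostic variable measured before randomisation raises the expected power of the treatment test and accounts for chance imbalance in that variable. The data will already be in hand. What is at stake is a modest amount of power on one of the two primary outcomes.

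**Working it through.** **1. The plan's own figure.** Inputs from Sample size {14}: control rate, "we might expect 30% of urgent dental care users to return for a planned dental care appointment"; a difference of 9 points after allowing for contamination; 80% power; alpha 0.025; 559 per group; 5% loss. Two-sided testing is assumed from the 97.5% confidence intervals.

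n = [z(0.9875)·√(2p̄(1−p̄)) + z(0.80)·√(p1(1−p1) + p2(1−p2))]² / d², with z values 2.2414 and 0.8416. The continuity correction multiplies n by (1 + √(1 + 4/(n·d)))² / 4.

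- 31% v 40%: n = 536.1, so 537; corrected 558.1, so **559**, an exact match.
- 30% v 39%: n = 529.0, so 530; corrected 551.0, so 552.
- Allowance for loss: 559/0.95 = 588.4, so 589; the plan rounds to 590.

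No covariate enters, so the stated 80% power does not rely on one.

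**2. Power with and without intention.** The strength of the link is an assumption. Set-up: one standard normal covariate, marginal rates 30% v 39%, two-sided alpha 0.025, no site effect, 8000 simulated trials per setting.

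| Assumed OR per SD | Power at 590 per arm, unadjusted → adjusted | Gain at 590 (points) | Gain at 559 (points) |
|---|---|---|---|
| 1.3 | 85.1% → 85.4% | 0.3 | 0.8 |
| 1.6 | 84.9% → 86.5% | 1.6 | 1.6 |
| 2.0 | 84.3% → 87.2% | 2.9 | 3.7 |
| 2.5 | 84.1% → 89.7% | 5.6 | 5.4 |

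The standard error of each paired gain is 0.2 to 0.3 points.

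**3. Where the gain comes from.** A second simulation (4000 trials per setting, 559 per arm) gives the mean log odds ratio b and its standard error:

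| Assumed OR per SD | Unadjusted b (SE) | Adjusted b (SE) | b/SE, unadjusted → adjusted |
|---|---|---|---|
| 1.25 | 0.3994 (0.1268) | 0.4043 (0.1276) | 3.15 → 3.17 |
| 1.5 | 0.3968 (0.1268) | 0.4124 (0.1293) | 3.13 → 3.19 |
| 2.0 | 0.3978 (0.1268) | 0.4389 (0.1334) | 3.14 → 3.29 |
| 2.5 | 0.3968 (0.1268) | 0.4642 (0.1375) | 3.13 → 3.38 |

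The standard error rises with adjustment, but the conditional log odds ratio rises more. With power ≈ Φ(b/SE − 2.2414), the row for 2.0 gives Φ(0.896) = 81.5% and Φ(1.049) = 85.3%, a gain of 3.8 points, in line with step 2.

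**4. Risk-difference scale.** Here the interval does narrow, by a factor √(1−R²): 0.995 at R² = 0.01, 0.975 at 0.05 and 0.949 at 0.10. Power at 559 per group (no continuity correction) goes from 82.3% at R² = 0 to 82.7%, 84.4% and 86.4%. An odds ratio of 2.0 per SD corresponds to R² of about 0.09.

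**The case against.** The strongest reply is that nothing here is wrong. Adjusting for site matches the stratified randomisation, the sample size never assumed a covariate gain, and the choice of one more covariate is a matter of judgement. All of that stands.

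The premise is also softer than it looks. The theory section reports a prediction about formed motivation, not a measured association between a questionnaire item and attendance at 12 months. Everyone enrolled has gone two years or more without planned care and is asked while seeking urgent care, so baseline intention may vary little. That stands too, and it is why the size is given only as a range.

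A reader might infer that the trial is short of power, that the reported odds ratio would gain a tighter interval, or that adjustment costs nothing and can do no harm. The documents and the working do not support these readings. The 559 reproduces without covariates and the odds-ratio standard error rises. The estimate also becomes conditional on the covariates, and missing baseline items could remove people from a denominator defined as all randomised participants. Chance imbalance is a small matter as well: the standard deviation of a chance standardised difference is √(2/590) = 0.06.

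Two objections carry less weight. The second analysis is described with an open word in section {20a}, and a full analysis plan exists that may say more; but section {20b} itemises the attendance covariates and intention is not among them. Intention is also a planned mediator, but mediation concerns values after allocation. Adjusting for a value taken before randomisation blocks no part of the effect.

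**Conclusion.** The point holds as an optional efficiency improvement. Both stated attendance models omit a variable that is collected before randomisation and that the protocol's own theory puts first. The gain from including it is from under 1 to about 5 points of power for assumed odds ratios of 1.3 to 2.5 per SD at 30% versus 39%, and close to nothing if intention varies little. The benefit lies in the power of the test, or in the precision of a standardised risk difference. There is no contradiction and no shortfall against the stated power.

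The size rests on the assumed strength of the link, a single normally distributed covariate, two-sided testing and no site effect in the simulations. The omission itself does not depend on these.

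**What to change.** Before the statistical team sees unblinded data, prespecify the following.

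- Add baseline intention and baseline MDAS as fixed covariates to the attendance model of section {20a}, beside the site random intercept.
- Keep the site-only model as a sensitivity analysis and report both odds ratios, ideally with a standardised risk difference.
- State a simple rule for missing baseline items, such as mean imputation or a missing indicator, so that all randomised participants stay in the denominator.

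If the primary model is to stay as it is, the minimum is to add baseline intention to the covariate list in section {20b}. That leaves the primary estimate untouched.

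The cost is a few lines in the analysis plan, or an amendment if it is already final, and no new data. The downside is that the primary odds ratio becomes covariate-conditional, somewhat further from 1 than the site-only one, and that missing baseline items need handling.

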**Methods:**

The RETURN intervention has been developed with substantial community co-production, to be delivered opportunistically in urgent dental care settings. This brief intervention is delivered by dental nurses and involves material relevant to the ‘in-group’ targeted. The material includes booklets relating to barriers to planned dental visiting with corresponding short video clips featuring local people and including a modelling element. Dental nurses are trained to have supportive and non-judgemental conversations, assisting patients to set personal goals and action plans, which are reinforced in a follow-up text within a few weeks. A randomised controlled trial will be undertaken in 3 types of sites: dental practices delivering urgent care (a) within working hours, (b) out of hours, and (c) in a Dental Hospital. The trial will recruit 1180 adult urgent dental care users over 12 months, who have not visited a dentist for a planned care appointment for 2 years or more and do not have a dentist who they visit for routine care. It aims to investigate the effectiveness and cost-effectiveness of the intervention and to explore whether the intervention has different effects across the socio-economic gradient. Participants will be followed up at 6, 12 and 18 months after randomisation. Co-primary outcomes are attendance at a dental practice for planned care within 12 months and self-reported oral health-related quality of life at 12 months.

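### Optional improvement: Holm's step-down rule would give the two primary outcomes the same 5% familywise control as the fixed 0.025/0.025 split, and never fewer rejections

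*Protocol article*

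**What the plan says.** The abstract names the two outcomes: "Co-primary outcomes are attendance at a dental practice for planned care within 12 months and self-reported oral health-related quality of life at 12 months". The statistical methods section ({20a}) fixes the multiplicity rule: "To allow for joint primary outcomes, the type I error rate will be controlled by setting" α = 0.025. It ties the intervals to that rule, so that "confidence intervals (CI) will be presented at 97.5% for both the primary outcomes", and then says "No other adjustments will be made for multiplicity".

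The sample size section ({14}) uses the same level. For attendance, "a sample size of 559 per group would give 80% power at" α = 0.025, and 5% loss brings this to 590 per group. For OHIP-14 it claims 80% power, also at 0.025, for 2.25 points with an SD of 11 and 20% loss.

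The article mentions no step-down procedure. It also does not say in words whether a positive trial needs one primary outcome or both.

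**The concern.** Under a fixed split each outcome is always judged at 0.025, even when the other has already been rejected. Once one null hypothesis is rejected at 0.025, only one remains that could be falsely rejected, and it can be tested at 0.05 without taking the familywise error above 5%. The fixed split leaves that allowance unused.

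Take attendance p = 0.01 and OHIP-14 p = 0.035. Under the stated rule OHIP-14 misses its threshold. Under Holm, with the same 5% familywise guarantee, both are established. Both outcomes are primary objectives, so the chance of establishing both matters to the trial.

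**Working it through.** **1. The plan's own figures.** Inputs from {14}: two-sided α = 0.025 (z = 2.241), power 80% (z = 0.842), a control rate of 30% against a target of 40%, and then this step: "we have reduced the difference we want to detect to 9 percentage points to allow for potential contamination". The article states neither the sidedness nor where the 9 points lie, so both are inferred from what reproduces its result.

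For 31% v 40%, the pooled-variance formula gives n = (2.241 × 0.6767 + 0.842 × 0.6737)² / 0.09² = 536.1, or 537. With the continuity correction, n/4 × (1 + √(1 + 4/(n × 0.09)))² = 558.1, or **559**, the stated figure. Placing the 9 points at 30% v 39% gives 552. One-sided versions give 437 to 465 and do not reproduce it. Loss: 559/0.95 = 588.4, or 589, against 590 stated.

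OHIP-14: 590 × 0.8 = 472 per group. SE = 11 × √(2/472) = 0.716, and 2.25/0.716 = 3.142. Power = Φ(3.142 − 2.241) = **81.6%**, against 80% stated. Sizing, tests and intervals therefore agree.

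**2. Familywise error.**
- Split: 0.025 + 0.025 = 0.05 at most. Under independence it is 1 − 0.975² = 0.0494.
- Holm, both nulls true: a false rejection needs the smaller p-value to be at or below 0.025, exactly as under the split, so the error is the same (0.0494 at correlation 0 and 0.0484 at 0.3, by simulation).
- Holm, one null true: it can be rejected only if its own p-value is at or below 0.05.

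The 5% bound therefore holds under any dependence.

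**3. Power, independent test statistics.** At 80% power the non-centrality is 2.241 + 0.842 = 3.083. Power at 0.05 is Φ(3.083 − 1.960) = 0.869, so the chance that p falls between 0.025 and 0.05 is 0.869 − 0.800 = 0.069.
- Both, split: 0.8² = 0.640.
- Both, Holm: 0.869² − 0.069² = 0.751. The subtracted term is the case in which neither p-value reaches 0.025.
- Each, Holm: 0.800 + 0.069 × 0.8 = 0.855.
- At least one, either rule: 1 − 0.2² = 0.960, because Holm's first step is the split's own test.

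**4. Power, correlated test statistics.** The article gives no correlation, so a range is assumed (4 million simulated pairs per row, each outcome at 80% power at 0.025).

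| Correlation | Each: split | Each: Holm | Both: split | Both: Holm | At least one: either rule | Holm rejects an outcome that the split does not |
|---|---|---|---|---|---|---|
| 0 | 80% | 85.6% | 64.0% | 75.1% | 96.0% | 11.1% |
| 0.3 | 80% | 84.9% | 66.6% | 76.5% | 93.4% | 9.9% |
| 0.5 | 80% | 84.6% | 68.8% | 77.9% | 91.3% | 9.1% |
| 0.8 | 80% | 83.7% | 72.9% | 80.4% | 87.1% | 7.5% |

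**5. Only one real effect.** The second step then opens only when the null outcome is falsely rejected at 0.025. The gain is about 0.069 × 0.025 = 0.0017, or 0.2 points. Simulation at correlation 0 agrees: 82.3% to 82.5% for attendance and 81.6% to 81.8% for OHIP-14, at the power the planned numbers give each without a continuity correction.

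**6. Effect on the intervals.** An outcome rejected only at the second step has p between 0.025 and 0.05, so its 97.5% interval includes no effect. The last column of the table shows how often this happens at the design effects. Two 97.5% intervals have joint coverage of 95.0% to 96.0% over these correlations; two 95% intervals have 90.2% to 92.2%.

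**The case against.** The strongest reply is that nothing here is wrong. The split is valid, prespecified and used consistently in the sizing, the tests and the intervals. The trial was sized at 0.025 and reaches its stated 80% for each outcome. The article sets no target for winning on both. Each decision can be read directly from its interval, which is a legitimate reason to prefer the split. All of this stands, and it is why the point is an improvement and not a correction.

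A reader might go further and infer that the split wastes power, and that Holm gives strictly more power at no cost. The documents do not support that. Power for at least one outcome is identical, the gain nearly vanishes if only one effect is real, and the article links its intervals to α, so Holm breaks a tie that the plan made on purpose.

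The size of the gain is also open to challenge. Independence is the favourable case; at a correlation of 0.8 the gain for both is 7.5 points, not 11.1. The planned OHIP-14 model adjusts for baseline, which the sizing ignores. If the baseline correlation were 0.3, 0.5 or 0.7 (assumed; not in the article), OHIP-14 power at 0.025 would already be about 85%, 92% or 98%, and Holm would add about 4.5, 3 or 1 points for that outcome. A reader might also infer from the rationale, in which oral health improves through attendance, that a modest OHIP-14 p-value is likely. The article does not show this.

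Finally, p = 0.035 would not be hidden: estimates, intervals and p-values to three decimals are reported, and the plan attaches no label of failure.

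**Conclusion.** The point holds as a cheap improvement to a sound rule. Holm keeps the 5% familywise bound and is never worse in rejections. At the plan's 80% power for each outcome, it adds about 4 to 6 points per outcome and about 7 to 11 points for establishing both, over assumed correlations of 0.8 down to 0.

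These gains require both effects to be real and of design size, and they shrink if the baseline adjustment lifts OHIP-14 power well above 80%. They should not be read as showing that the trial is underpowered or that its error control is faulty: the article's figures reproduce and its multiplicity rule does what it claims.

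**What to change.** In {20a} and the SAP, replace the fixed split by Holm for the two primary outcomes: test the smaller p-value at 0.025 and, if it is significant, the other at 0.05. State that success on either outcome is a positive finding. Splitting α already implies this, but the term co-primary can be read as requiring both.

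Keep the 97.5% intervals for both outcomes and add a 95% interval for the outcome tested at 0.05. Say in the report that the decision rests on the Holm-ordered p-values, that an outcome rejected only at the second step will have a 97.5% interval that includes no effect, and that the added 95% interval does not preserve 95% joint coverage.

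Make the change before the statistical team has access to unblinded data, the same limit that {17a} sets for writing the SAP. It costs a protocol amendment in a trial that is already recruiting, with the sponsor and ethics committee approval that {25} requires, and one more interval to report. No participants are added and the sample size does not change.
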